## Abstract

**Background:**

Femoroacetabular impingement (FAI) is an important cause of hip pain in young and active individuals and occurs as a result of size and shape mismatch between the femoral head and acetabulum. Open physes in children can make hips more susceptible to injury, and high impact forces have been suggested to affect the developing femur. The diagnosis of FAI has recently risen, especially within adolescent populations, and there is an increasing trend towards year-round participation in sports with early specialization. The PREVIEW study is an international longitudinal study designed to determine the association between sport specialization in adolescence and the development of hip impingement.

**Methods:**

This is a multicentre prospective cohort study evaluating 200 participants between the ages of 12–14 that include sport specialists at the moderate to vigorous physical activity (MVPA) level and non-sport specialists at any activity level. We will monitor physical activity levels of all participants using an activity log and a wrist-mounted activity tracker, with synced data collected every 3 months during the study period. In addition, participants will be evaluated clinically at 6, 12, and 18 months and radiographically at the time of enrolment and 24 months. The primary outcome is the incidence of FAI between groups at 2 years, determined via MRI. Secondary outcomes include hip function and health-related quality of life between subjects diagnosed with FAI versus no FAI at 2 years, as determined by the Hip Outcome Score (HOS) and Pediatric Quality of Life (PedsQL) questionnaires.

**Discussion:**

It is important to mitigate the risk of developing hip deformities at a young age. Our proposed prospective evaluation of the impact of sport activity and hip development is relevant in this era of early sport specialization in youth. Improving the understanding between sport specialization and the development of pre-arthritic hip disease such as FAI can lead to the development of training protocols that protect the millions of adolescents involved in sports annually.

**Trial registration:**

PREVIEW is registered with clinicaltrials.gov (NCT03891563).

## Background

**Femoroacetabular impingement (**FAI) can cause hip pain and may lead to the development of osteoarthritis of the hip later in life. Some cross-sectional studies have estimated that the prevalence of hip impingement ranges from 14 to 17% among asymptomatic young adults to almost 95% among competitive athletes [1–3]. FAI occurs as a result of a size and shape mismatch between the femoral head and the acetabulum. FAI is typically classified into 2 subtypes; cam-type (a misshaped femoral head) or pincer type (an over covered or deep socket). Most adult patients (18+ years) have a combination of both types of impingement [4]. With FAI, the abnormal femoral head and acetabular rim of the hip joint collide or “impinge” during movements such as hip flexion and rotation [5]. Typically, patients with this condition experience hip pain and loss of hip function. The development of hip pain in this manner serves as an indicator for early cartilage and labral damage, potentially resulting in hip osteoarthritis [5].

The incidence of FAI has recently risen across all age groups, but it has been especially notable within paediatric, or more specifically, adolescent populations [6]. In the adult, FAI is most commonly attributed to an “idiopathic anatomic variant” [6]. In the paediatric population, implicated causes of FAI have included genetics, subclinical paediatric hip disease, and stresses applied to the hip joint from certain high-intensity sports [7]. According to Packer et al., there is no definitive evidence that FAI is transmitted genetically, and in otherwise healthy children, there is growing evidence that FAI has a higher prevalence in athletes who performed at a high level during adolescence [8–11].

High impact activities in combination with intensity of various kinds have been shown to affect the developing femur [12]. Among children, open physes and growing cartilage make them more susceptible to injury and shear forces that can result in premature physeal arrest, apophyseal avulsion fractures, and chondral injuries [13]. A higher prevalence of cam deformities (> 50%), both symptomatic and asymptomatic, has been shown in adolescent athletes that play ice hockey, basketball, and soccer when compared to controls that did not play sports [7, 10, 11, 14–17]. These sports involve repetitive deep flexion, flexion-adduction or extension-abduction movements, which bring the cam lesion on the femoral head or the pincer lesion on the acetabulum into conflict [6]. Therefore, participating in high impact sports during growth likely plays an important role in the development of hip deformities. This is concerning given: a) the increasing trend toward year-round participation in youth sports with early specialization and b) FAI has been shown to predispose patients to the progression of hip osteoarthritis [18–21]. Still, most studies in the current literature that evaluate the relationship between sports and the development of FAI are relatively small, retrospective case-controls and the most recent evidence demonstrates conflicting results regarding how and when primary FAI develops in relation to skeletal maturity [7, 22]. Accordingly, the current literature notes the need for longitudinal or prospective magnetic resonance imaging (MRI) studies to understand the etiology of primary FAI development to identify preventive strategies, delineate radiographic values, define specific indications for operative management, and examine long-term outcomes to determine optimal management [7, 12].

### Study objectives

The primary research objective is to determine if sport specialization at the moderate-to-vigorous physical activity (MVPA) level [23–27] is associated with the development of both symptomatic and asymptomatic FAI (i.e. cam, pincer, or mixed-type) in adolescents (ages of 12–14 years) at 2 years post-enrollment determined via MRI.

The secondary research objectives are to determine if the presence of FAI is associated with changes in hip function and health-related quality of life (HRQL) at 2 years post-enrollment determined via the Hip Outcome Score (HOS) and Pediatric Quality of Life (PedsQL) questionnaires.

## Methods

### Study design

This is a longitudinal cohort study of 200 participants between the ages of 12 and 14 (i.e. critical age of development of the femoral head and neck). Participants will be evaluated clinically at enrollment and 6, 12, 18, and 24 months and radiographically (with MRI) at baseline and 24 months. Activity will be tracked every 3 months from enrollment to final follow-up at 2 years. Participants will be recruited from experienced hip surgeons and sports medicine researchers at multiple international clinical sites. We will observe the incidence of radiographic FAI, as determined by MRI of the hip, and evaluate hip function and HRQL using the HOS and PedsQL, respectively. Ethics approval for this study was granted by the Hamilton Integrated Research Ethics Board (Version D1.0, 1-August-2019, HIREB #7829). Any protocol amendments will be submitted to HIREB and communicated to all participating sites for submission their site-specific ethics boards.

### Participant selection

#### Eligibility criteria

The inclusion criteria are: 1) asymptomatic males and females between the ages of 12–14 years; 2) ability to speak, understand, and read the language of the clinical site; and 3) provision of informed child assent (if applicable) and parental consent.

The exclusion criteria mainly preclude known confounding factors that would impede the evaluation of the etiology of a hip deformity. These include: 1) hip is mature (i.e. closed physes) based on the baseline MRI scan; 2) hip complaints or pain in the hip; 3) previous trauma to the hip; 4) previous surgery on the hip; 5) significant medical co-morbidities (requiring daily assistance for activities of daily living); 6) history of or ongoing paediatric hip disease (Legg-Calve-Perthes; slipped capital femoral epiphysis, hip dysplasia); 7) participants that have contraindications and/or are unwilling to undergo an MRI (e.g. claustrophobia); 8) participants who will likely have problems, in the judgment of the investigator, with maintaining follow-up; and 9) any other reasons the investigator feels is relevant for excluding the subject (e.g. participant is planning to move in the next 2 years, unreliable access to transportation to attend follow-up visits, etc.).

#### Participant recruitment and screening

The study activities at each participating clinical site will be led by experienced hip surgeons and sports medicine physician researchers. However, because we are looking for healthy volunteers, participants might not be exclusively recruited from the co-investigators’ clinics. Instead, we will use several recruitment strategies that have proven successful in our pilot study. These include: 1) posting study flyers throughout each participating institution; 2) distributing study flyers to grades in the eligible age range at school boards in the regions of the recruiting institutions; and 3) having the co-investigators reach out to community coaches and competitive sport organizations and clubs, and presenting the study to the organizers, parents, and adolescent athletes. Potentially eligible subjects will be approached along with their parents/guardians for consent for participation.

### Study exposure

The study groups will be defined by ‘exposure’ to varying levels of physical activity (i.e. exposure variables) and include sport specialists at the MVPA level (group 1) and non-sport specialists at any activity level (group 2).

#### Defining sport specialization

Sport specialization will be defined according to the American Orthopaedic Society for Sports Medicine (AOSSM) and American Medical Society for Sports Medicine (AMSSM) early sport specialization criteria (Table 1) [28, 33]. At the baseline/enrollment visit, we will collect information about any current sport participation, including type(s) and frequency, for each participant. One week prior to each follow-up visit, we will ask participants and their parent(s) to complete a daily activity log to record all types of sport activity the participant engaged in (e.g. games, practices, both organized and unorganized), or lack thereof.

**Table 1 Tab1:** Definition of study groups according to objective measurement and guideline criteria

Study group	AOSSM criteria [28]	Activity tracker criteria	Duration
Group 1: Sport specialist, MVPA	1. Participation in intensive training and/or competition in organized sports greater than 8 months per year (essentially year round) [29] 2. Participation in **1 sport** to the exclusion of participation in other sports (limited free play overall) [30] 3. Involving prepubertal (seventh grade or roughly age 12 years) children.	Greater than 180 accumulated minutes of MVPA [31, 32] during participation in one sport type across one week of activity tracking	Meets criteria within either one or both years of follow-up
Group 2: Non-sport specialist, any activity level	1. Participation in **more than 1 sport** at any physical activity level **OR** 2. Participation in **none or low** training and/or competition in organized sports for any period of time. 3. Involving prepubertal children.	Greater than or less than 180 accumulated minutes of MVPA across one week of activity tracking	Meets criteria during both years of follow-up

*AOSSM* American Orthopaedic Society for Sports Medicine, *MVPA* moderate-to-vigorous physical activity

#### Defining activity level

We will cross-reference the activity log with data from an objective wrist-worn activity tracker (Garmin® Vivofit 4) to define sport and other activity intensity [34]. The Vivofit is a small, lightweight, waterproof activity tracker with high validity (relative to reference measures of physical activity and direct observation), high reliability, low reactivity in children, and has been used successfully in multiple paediatric physical activity studies [26, 35–37]. The Vivofit utilizes accelerometer measurements to calculate the Metabolic EquivalenTs (METs) of energy expenditure, where activity greater than 3 METs corresponds to MVPA. The categorical activity output includes data for sedentary, fairly active, and MVPA levels. Relevant data also includes duration of MVPA and number of total active minutes per day [38]. We will use the cut-off of ≥180 min [31, 32] of MVPA per week detected by the tracker during recorded sport participation (as per the activity log) to define the MVPA level in group 1 (Table 1). The use of the activity tracker, in conjunction with self-reported activity logs has been shown to be accurate in estimating energy expenditure in adolescents [39, 40].

One week following the baseline visit and 1 week prior to each follow-up visit, participants will wear the tracker on their wrist for a full week and to sync it with a paired tablet or cellular phone. Measuring total ‘volume’ physical activity at several time points by one-week intervals is a standard methodology used in several paediatric physical activity studies [25–27]. The combination of the activity measures and criteria described above will be used to define the study groups as per Table 1. The study groups will be defined at the completion of follow-up given participant activity levels may change over time.

### Study outcomes

#### Primary outcome

The primary outcome is the incidence of radiographic FAI between groups at 2 years, as determined by the dedicated MRI of the hip (Table 2). We will identify both symptomatic and asymptomatic cases, where asymptomatic FAI can become symptomatic in young adulthood, and/or could be associated with idiopathic osteoarthritis later in life [41].

**Table 2 Tab2:** Criteria for defining FAI types

FAI type	Criteria
Cam	1. Alpha angle is > 55°; 2. Anterior head-neck offset < 10 mm; 3. Anterior head-neck offset ratio < 0.15 **Must meet 2/3 criteria to be considered cam impingement*
Pincer	1. Acetabular depth < 3 mm; 2. Lateral centre-edge angle > 39°; 3. Acetabular anteversion (in the upper third of the femoral head) < 0° **Must meet 2/3 criteria to be considered pincer impingement*
Mixed	**Must meet 2/3 criteria each for cam and pincer impingement (as per above) to be considered mixed impingement*

*FAI* Femoroacetabular impingement

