#### Outcome measures

Participants will complete the study questionnaires and undergo a physical examination (at baseline and 6, 12, 18, and 24 months) and MRI (at baseline and 24 months) of their dominant hip. Participants will sync their activity tracker data and send their activity log (at baseline and every 3 months until final follow-up at 2 years) (Table 3).

**Table 3 Tab3:** Schedule of events for the PREVIEW study

Data collection	Enrollment	3 M	6 M	9 M	12 M	15 M	18 M	21 M	24 M
Screening and informed consent	●								
Enrolment data (Demographics)	●								
Physical hip examination	●		●		●		●		●
MRI	●								●
Follow-up form	●		●		●		●		●
Activity tracker wear & synchronization	*	x	x	x	x	x	x	x	x
Activity log	*	x	x	x	x	x	x	x	x
Hip Outcome Score (HOS)	●		●		●		●		●
Pediatric QoL Inventory (PedsQL)	●		●		●		●		●
Adverse events			●		●		●		●

*M* months, *MRI* Magnetic Resonance Imaging, * = 1-week post-enrollment/baseline visit, x = 1-week prior to visit

The physical examination will include range of motion (ROM) measurements in all planes documented in the supine and prone positions by a blinded research assistant (using a goniometer), as well as response of provocative hip tests on both hips [44]. Symptomatic FAI in adolescents is typically characterized by anterior hip pain aggravated by flexion activities, decreased hip internal rotation, and a positive impingement sign [7]. We will define symptomatic FAI using the following criteria: 1) positive impingement with groin pain based on flexion, adduction, and internal rotation (FADIR) test, and 2) decreased ROM: internal rotation of the hip when compared to the contralateral side by 5 degrees [45, 46].

We will use a non-contrast three dimensional (3D)-volumetric interpolated breath-hold examination (VIBE) sequence MRI [47]. This protocol has been used to document FAI-related morphology and eliminates the use of intra-articular contrast injections. All MRI and physical examination information will be provided to an independent radiologist adjudicator to determine the incidence of cam, pincer, or mixed-type FAI according to the pre-specified criteria (Table 2). We will also document the change in cartilage volume, labral pathology, herniation pits on the femoral neck, and the extent of physeal closure as these variables may predict future hip osteoarthritis [44].

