### Study committees and monitoring

The Steering Committee will provide guidance and direction to the overall study. Specific responsibilities of the Steering Committee include reviewing and approving the study protocol and working together to resolve any challenges that arise during the study. The Steering Committee will also be supported by several Advisory Committees including: radiology, orthopaedic surgery, physiotherapy/training, and paediatrics and rehabilitation medicine. These Advisory Committees consist of individuals who are experts within their fields and have committed time to provide advice to the Steering Committee throughout the initiation and conduct of this study. An independent adjudication committee blinded to each participant’s activity level, will determine the incidence of cam, pincer, or mixed-type FAI (primary outcome) and evaluate all adverse events reported during the study. Ongoing remote and in-person clinical site monitoring will be performed by experienced Methods Centre personnel (Fig. 1).

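### The adjudicator who applies the MRI-only FAI criteria is also given the physical examination results; in addition, two of the three cam criteria are nested, which calls for a prespecified sensitivity analysis

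*Protocol article*

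**What the plan says.** The primary outcome is FAI on MRI at 2 years, classified by Table 2 (Primary outcome). For cam type, the table lists "Alpha angle is > 55" degrees as criterion 1 and "Anterior head-neck offset < 10 mm; 3. Anterior head-neck offset ratio < 0.15" as criteria 2 and 3, with the rule "Must meet 2/3 criteria to be considered cam impingement". The denominator of the ratio is not given. The three pincer criteria are also imaging measurements, and mixed type combines the two rules.

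The same section adds: "We will identify both symptomatic and asymptomatic cases". Under Outcome measures, symptomatic FAI is defined from the examination: a positive FADIR test with groin pain, and internal rotation reduced by 5 degrees against the other side.

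On who classifies the hip, Outcome measures says: "All MRI and physical examination information will be provided to an independent radiologist adjudicator to determine the incidence of cam, pincer, or mixed-type FAI", using Table 2. Study committees and monitoring gives the same task to a committee that does not know the participant's activity level.

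**The concern.** There are two separate issues, and the first carries more weight.

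**What the adjudicator sees.** None of the Table 2 criteria uses the examination, yet the person applying them receives it. Alpha angle, offset and the pincer measurements all have borderline values. A reader who knows that the hip is painful, or that it rotates less, may settle those towards FAI. The secondary analyses then compare HOS and PedsQL at 24 months between participants with and without FAI. If hip pain has helped to assign the FAI label, part of any difference in hip function follows from how the label was made.

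**What the cam rule requires.** A 2-of-3 rule suggests that two distinct signs agree. Criteria 2 and 3 are one measured offset expressed in two ways, so one of the three possible pairs may give no confirmation beyond the offset itself.

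**Working it through.** **The plan's own figure.** Inputs from Sample size calculation: 40% versus 15%, two-sided alpha 0.01, power 80%.

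- Mean proportion: (0.40 + 0.15)/2 = 0.275.
- Uncorrected n = [2.576 × √(2 × 0.275 × 0.725) + 0.842 × √(0.40 × 0.60 + 0.15 × 0.85)]² / 0.25² = 73.05, rounded up to 74.
- With continuity correction: (73.05/4) × [1 + √(1 + 4/(73.05 × 0.25))]² = 80.9, rounded up to 81.

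The stated 81 per group is reproduced. The sample size is not in dispute.

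**The adjudicator: the sections side by side.**

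- Primary outcome: the label is radiographic and rests on Table 2. Information needed: MRI only.
- Outcome measures: the symptomatic label rests on FADIR with groin pain and on internal rotation. Information needed: the recorded examination, for hips already classified as FAI.
- Outcome measures: both sets of information go to the adjudicator, with no order of reading stated.
- Study committees and monitoring: the stated blinding is to activity level. It does not cover the examination or symptoms.

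The two labels can therefore be separated, and the blinding described does not separate them. The primary comparison would be biased between groups only if examination results track sport exposure. The secondary comparison is exposed more directly, because hip pain can affect both the reading and the HOS.

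**The cam rule.** Assumption: ratio = offset / femoral head diameter D.

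- Criterion 3 means offset < 0.15 × D. This lies below 10 mm whenever D < 10/0.15 = 66.7 mm.
- Over an assumed range of head diameters:

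| D (mm) | 35 | 40 | 45 | 50 | 55 | 60 |
|---|---|---|---|---|---|---|
| Criterion 3 as an offset (mm) | < 5.25 | < 6.0 | < 6.75 | < 7.5 | < 8.25 | < 9.0 |

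- So criterion 3 brings criterion 2 with it. The pairs (2, 3) and (1, 3) are both contained in ratio < 0.15. The pair (1, 2) stays as it is.
- The rule reduces to: ratio < 0.15, or alpha > 55° with offset < 10 mm.

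With an assumed 44 mm head, 0.15 × 44 = 6.6 mm. An offset below 6.6 mm is a cam case at any alpha angle. An offset from 6.6 mm to just under 10 mm meets one criterion and still needs alpha > 55°.

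**How many hips take the route without alpha.** The document gives no distribution. Assuming a normal ratio with SD 0.03:

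| Assumed mean ratio | (0.15 − mean)/0.03 | P(ratio < 0.15) |
|---|---|---|
| 0.18 | −1.00 | about 16% |
| 0.20 | −1.67 | about 5% |
| 0.22 | −2.33 | about 1% |

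These are upper limits for hips that are cam cases because of the nesting, since some of them will have alpha > 55° as well.

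**What label error would cost, as an illustration only.** Assume sensitivity 1, the same specificity in both groups, 81 per group and no continuity correction. The observed rate is p + (1 − p)(1 − specificity).

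| Assumed specificity | Rates | Odds ratio | Power |
|---|---|---|---|
| 1.00 | 40% vs 15% | 3.78 | 0.85 |
| 0.95 | 43% vs 19.3% | 3.16 | 0.76 |
| 0.90 | 46% vs 23.5% | 2.77 | 0.67 |

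Nothing in the document says which row applies.

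**The case against.** The examination data have a stated use: cases must be labelled symptomatic or asymptomatic. FAI type is tied to numeric limits fixed in advance, adjudication is blinded to exposure, and range of motion is measured by a blinded assistant. Nothing says that HOS or PedsQL scores reach the adjudicator. Order of reading is often left to an adjudication charter. All of this limits the likely effect to borderline readings. It does not remove the point, because the article states what the adjudicator receives, and the symptomatic label can be added after the MRI has been read.

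On the cam rule, a reader might infer more than the document supports:

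- *That the classification is distorted, or that false-positive cases enter.* The document gives no reference standard by which a hip with ratio < 0.15 and alpha of 55° or less is wrongly called cam. Requiring alpha is a choice of case definition.
- *That any low offset makes a case.* Only an offset below 0.15 × diameter does so, and the ratio needs head diameter as well.
- *That smaller hips qualify more easily.* The route that bypasses alpha is scaled to head size. The fixed 10 mm limit matters only on the other route, where alpha > 55° is still required.
- *That the primary outcome should be redefined.* The 40% and 15% rates come from pilot participants who are rolled into the main study. Changing the definition now would be a change made after outcomes were seen, and it would reopen the sample size.

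These objections stand. They limit the cam point to a sensitivity analysis.

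**Conclusion.** The adjudicator point holds as stated in the document. The examination goes to whoever applies criteria that do not use it, and blinding to activity level leaves that path open. It could influence borderline primary labels and build in part of the association between FAI and HOS or PedsQL. Its size cannot be derived.

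The nesting of cam criteria 2 and 3 holds if the ratio is offset over femoral head diameter and the head is under 66.7 mm. The share of hips affected runs from about 1% to at most about 16% under assumed distributions. Whether that adds misclassification, and how much, cannot be settled from the document. Error from the cam rule would be expected to be mainly the same in both groups, so it would weaken the odds ratio and cost power; it would not be expected to create an association.

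The mismatch between one radiologist and a committee is minor wording with no shown effect on results, but it should be reconciled.

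**What to change.** 1. In Outcome measures, state that Table 2 is applied to the MRI alone, blinded to examination, symptoms and activity level, and that symptomatic status is derived afterwards from the recorded examination.
2. Name the same adjudication body in Outcome measures and in Study committees and monitoring.
3. State the denominator of the offset ratio under Table 2.
4. Keep the primary definition. Prespecify a sensitivity analysis of the primary outcome in which offset and offset ratio count as one criterion that must be met together with alpha > 55°. Say how the single criterion is met: if either limit suffices, the analysis removes exactly the cam classifications with ratio < 0.15 and alpha of 55° or less.

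Cost: items 1 to 3 are wording and order of work, with the same scans, measurements and reader. Item 4 is one extra analysis with fewer cam cases, so it will be less precise. The primary definition, the pilot rates and the 81 per group are untouched.
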